## Abstract

**Abstract:**

The magnitude of the tradeoff between recall rate (RR) and cancer detection rate (CDR) in breast-cancer screening is not clear, and it is expected to depend on target population and screening program characteristics. Multi-reader multi-case research studies, which may be used to estimate this tradeoff, rely on enriched datasets with artificially high prevalence rates, which may bias the results. Furthermore, readers participating in research studies are subject to “laboratory” effects, which can alter their performance relative to actual practice. The *Recall and detection Of breast Cancer in Screening* (ROCS) trial uses a novel data acquisition system that minimizes these limitations while obtaining an estimate of the RR-CDR curve during actual practice in the Dutch National Breast Cancer Screening Program. ROCS involves collection of at least 40,000 probability-of-malignancy ratings from at least 20 radiologists during interpretation of approximately 2,000 digital mammography screening cases each. With the use of custom-built software on a tablet, and a webcam, this data was obtained in the usual reading environment with minimal workflow disruption and without electronic access to the review workstation software. Comparison of the results to short- and medium-term follow-up allows for estimation of the RR-CDR and receiver operating characteristics curves, respectively. The anticipated result of the study is that performance-based evidence from practice will be available to determine the optimal operating point for breast-cancer screening. In addition, this data will be useful as a benchmark when evaluating the impact of potential new screening technologies, such as digital breast tomosynthesis or artificial intelligence.

**Key Points:**

*• The ROCS trial aims to estimate the recall rate–cancer detection rate curve during actual screening practice in the Dutch National Breast Cancer Screening Program.*

*• The study design is aimed at avoiding the influence of the “laboratory effect” in usual observer performance studies.*

*• The use of a tablet and a webcam allows for the acquisition of probability of malignancy ratings without access to the review workstation software.*

**Supplementary Information:**

The online version contains supplementary material available at 10.1007/s00330-022-08820-5.

## Introduction

Combined with improvements in treatment, mammography-based screening has been credited with an important decrease in breast cancer mortality over the last two decades [1]. Nonetheless, screening mammography itself is not a perfect diagnostic test; it invariably involves a tradeoff between sensitivity and specificity, or equivalently, the unconditional outcomes of recall and detection rates. Ideally, when screening is performed as part of a regional or national program, this tradeoff should be selected to balance the outcomes according to the priorities of the program, the characteristics of the target population, and the procedures used for screening.

In the Netherlands, a publication by Otten et al [2] has been highly influential in establishing guidelines for radiologist performance in screening mammography. This study led the screening program to adopt a target recall rate of 2%, with a predicted cancer detection rate of 4.52 women per 1000 screens. These guidelines remained in place as the program transitioned to digital mammography (DM). Shortly after this transition, in 2011, the recall rate was close to this value (2.14% with 95% CI: 2.12–2.17%), although the detection rate (6.3/1000 with 95% CI: 6.2–6.5) was 40% higher than what was anticipated from the Otten study. This difference may be attributable to the “laboratory” nature of the study, in which a curated set of cases was used to evaluate reader performance with the knowledge that reader decisions did not involve patient management.

Over the years since, the recall rate in the Netherlands has varied, typically with somewhat higher observed values than the recommendation. In 2016, the program recall rate was 2.43%, with a corresponding detection rate to 7.0 cancers per 1000 women screened [3]. In the latest available complete statistics, from 2018, the recall rate has decreased to 2.23% with a corresponding cancer detection rate of 6.7/1000 [3]. These deviations from the expected recall and cancer-detection levels, combined with interest in new approaches to screening, such as artificial intelligence and digital breast tomosynthesis, have motivated further examination of the tradeoff between recall and cancer-detection rates in breast cancer screening. The purpose of the *Recall and detection Of breast Cancer in Screening* (ROCS) trial is to characterize the underlying relationship between these measures in screening practice.

Audit data from screening practice is commonly used for determining program performance. However, audit data produces a single estimate of the recall/detection pair, and therefore has limited value for evaluating the tradeoff between recall and detection rates. To evaluate this tradeoff, a probability of malignancy (PoM) score is needed that can be compared to different thresholds for recall, but these are not obtained as part of screening practice. In essence, this PoM reflects the reader’s internal decision process, before applying a threshold to dichotomize their decision into a recall/no-recall outcome [4–6]. Laboratory studies allow for collection of PoM scores, which are then used to generate receiver operating characteristic (ROC) curves that quantify the tradeoff between sensitivity and specificity. ROC performance can be readily converted into estimates of recall and detection rates with knowledge of disease prevalence. However, these studies are potentially subject to so-called *laboratory effects* that may lead to biased results. Typically, laboratory studies involve the enrichment of the testing set with additional examples of positive cases, which can also lead to prevalence biases in reader responses [7].

The ROCS trial avoids the potential issue of laboratory effects and the difficulty of extrapolating current performance into predictions of performance at different operating points by using a novel system to acquire PoM scores during actual screening practice. The system is designed to minimally interrupt clinical workflow, and to automatically associate the PoM response with the case identifier. In this Special Report, we present the design of the ROCS trial, aimed at determining the performance tradeoffs for digital mammography interpretation in the actual breast cancer screening environment of the Dutch National Breast Cancer Screening Program. At present, the first stage of data acquisition, the accrual of reader case scores during screening is completed, and the results of this stage are presented. The second and final stages of data acquisition, involving the determination of the ground truth for the recalled cases and, then, after the 2-year waiting period, for the non-recalled cases, are ongoing.

## Materials and methods

No external funding was needed or obtained for the performance of this study. The study was waived of the requirement of ethics approval and informed consent by the research ethics committee of the Radboud University Medical Center.

### Overall study design

The primary aim of the ROCS trial is to estimate the trade-off between recall rate (RR) and cancer detection rate (CDR) by estimating the RR-CDR curve for the average radiologist in the Dutch National Breast Cancer Screening Program directly from screening interpretations. Secondary endpoints include estimating the ROC curve for the average breast radiologist during actual screening interpretation and determining if reader performance changes as they progress within one reading session, as previously reported [8].

For this, ROCS involves obtaining a PoM rating from screening radiologists (*n* = 20) for each and every case (*n* = 2,000 per radiologist) they interpret during several screening reading sessions (approximately *n* = 8), with minimal interruption or diversion from their usual reading workflow. The outcomes of the cases included in the ROCS trial will be obtained from short-term (1 year) follow-up of the recalled cases via the screening organization and long-term (2 years) follow-up via the Netherlands Cancer Registry.

### Study cases

The digital mammography cases included in ROCS involved cases acquired and interpreted as part of the Dutch National Breast Cancer Screening Program. In the Netherlands, the screening program invites all women between the ages of 50 and 75 to be screened for breast cancer with digital mammography nominally every 2 years, with this period having some regional variability. All image acquisitions, involving the standard cranio-caudal (CC) and medio-lateral oblique (MLO) views, are performed at dedicated screening centers equipped with the same imaging systems (Selenia, Hologic Inc.). The systems are all under the same quality control protocol, performed by the same group of physicists at the Dutch Expert Centre for Screening (LRCB) for the nationwide program. The technologists that acquire all images are specifically trained and undergo regular refresher education and auditing on screening mammography. Cases are interpreted in batches, at dedicated reading centers, usually within 1 or 2 days of acquisition. All reading is performed by certified screening radiologists, who undergo additional periodic training and evaluation to be a part of the screening program. Throughout the program, the mammograms are viewed on a SecurView mammography screening workstation (Hologic Inc.) with dual-head 5-megapixel monitors (Coronis 5MP Mammo, MFGD 5621 HD, Barco). The mammography monitors used are also tested by the physicists of the LRCB, as per established protocols.

Although the Dutch National Breast Cancer Screening Program involves independent double reading of all cases with consensus or arbitration for disparate decisions, ROCS is focused on individual reader performance. This is because the overall aim of this endeavor is to gather the evidence needed to inform the setting of new performance guidelines for radiologists. Therefore, all performance estimates are performed at the level of individual readers, and then these are aggregated into results for the screening program as a whole. In addition, due to the nature of screening, all acquisition and analysis are performed at the per case level, as opposed to per breast or per lesion.

For ROCS, a total of 40,000 cases were needed and were aimed to be included, as determined by the sample size calculation, described below. All cases included for interpretation were eligible for inclusion, with no exclusion criteria. There was no attempt to order the cases or to balance the case sets for different properties of the screened women.

### Study radiologists

All radiologists participating in the Dutch National Breast Cancer Screening Program were considered eligible, since they already have to meet minimum training, continuing certification, and case volume requirements (*n* > 3,000 screens per year) to participate in the program. To maximize the diversity in geographic, socio-economic, and other factors in the screening cases, radiologists from five different reading centers around the country were targeted to participate in ROCS. In total 21 radiologists were recruited to participate in the study, since we aimed to recruit at least 20 radiologists.

### Data acquisition

During interpretation of each case of a screening batch, a case-based PoM rating was obtained from the interpreting radiologist after their review of the case with minimal disruption of the workflow. This had to be achieved without modifying the image review software, due to certification requirements for medical software. In addition, it was not feasible to have a research assistant recording, manually or electronically, case numbers and PoM ratings from the readers during their image interpretations.

Therefore, a simplified graphical user interface (GUI) on a tablet (Surface Pro 4, Microsoft Corp.) was developed and implemented for this study (Fig. 1). The interface consists mainly of a horizontal bar across the entire touchscreen-enabled tablet, which the reader swipes vertically across at the horizontal position that reflects their level of suspicion of a malignancy being present. If the case raises no suspicion, then the reader will swipe vertically across the left-most region of the bar, labelled “normal,” while certainty of cancer present would result in a vertical swipe across the right-most region, labelled “malignant.” The center of the bar is labelled “uncertain.” The horizontal location of the swipe is encoded as a quasi-continuous score ranging from −100 (*normal*) to +100 (*malignant*), with zero in the center (*uncertain*), resulting in 201 possible PoM scores. This large rating scale was patterned after prior work [9]. The radiologists were instructed to swipe to the left of center if they did not recall the case, and to the right of center if they did. By displaying only the bar with the three descriptors with no numbering, and the bar consisting of a continuous gradient from green to red color, to the reader the scoring scale consisted of a continuous scale. The encoded scores are then automatically saved by the tablet.

**Fig. 1 Fig1:**
[figure not shown]
(Left) ROCS trial hardware setup, showing the tablet the radiologists use to input their determined PoM rating and the webcam aimed at the third monitor to record the case identification number. (Right) The tablet graphical user interface used to record the PoM on the colored horizontal bar, also showing the image to be captured by the webcam on the top left corner for confirmation that the camera is correctly positioned and in focus. Note that the mammogram shown in this figure has been de-identified

To ensure that the recorded ratings are paired with the correct screening case, the tablet is connected to a webcam (C922 Pro Stream Webcam, Logitech), positioned so that a photograph of the area of the screen that displays the *Invitation Number* is acquired. To minimize the added process, no confirmation of the PoM selection nor tapping on a *Save* nor *Next* button is necessary. Once a rating is entered, the GUI counts down three seconds, and unless the user stops the countdown, the data is saved, and the GUI is ready for the next case. If the radiologist wanted to change the rating entered, they were instructed to re-enter a rating, and only the last one given for the same case would be considered. Together with the photo and the PoM rating, the program automatically records the time the rating is entered, allowing for analysis of timing.

A pilot test was performed by having one participating screening radiologist use the tablet during one of his regularly scheduled screening reading sessions. The session involved the reading of 164 cases, and aside from the use of the tablet as described, all other characteristics of the session were normal. Comparison of the total time for this session to previous ones resulted in an estimated slow-down by the use of the tablet of 8%.

### Study endpoints

The primary endpoint of ROCS is the estimation of the curve describing the relationship between recall rate and cancer detection rate for the average reader in the Dutch National Breast Cancer Screening Program. From this curve, it would be possible to determine the benefit, or lack thereof, in increased number of cancers detected at screening due to an increase in the recall rate. In addition to the PoM ratings from the exam interpretations, constructing this curve involves obtaining the outcome of the cases recommended for recall by each participating radiologist. This data is available through the screening organization. As per the programmatic definition, breast cancer diagnosed within 12 months of the woman being recalled from screening is defined as a screening-detected cancer.

As related secondary endpoints of the ROCS trial, two different average-reader ROC curves will be estimated to better characterize performance of readers in the screening program. The first will be constructed considering all cancers as defined by the program, i.e., all breast cancers diagnosed within 24 months after the date of screening acquisition. Interval cancer cases will be identified through linkage with the Netherlands Cancer Registry after the necessary waiting period. However, it is known that approximately half of all interval cancers are visible at the prior screening [10]. To identify these, all interval cancer cases will be reviewed by a panel of experts and graded as the cancers being *not visible*, *present with minimal signs*, or as *missed*. This is a common procedure in the Dutch National Breast Cancer Screening Program, performed for education and quality assurance purposes. Additional ROC curves will be constructed, one excluding interval cancers deemed *not visible* and one involving only invasive cancers.

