### Description of the model for determining sample size

A model of breast-cancer screening was derived and used to evaluate the number of radiologists and screening exams that would generate a RR-CDR difference curve of sufficient precision. The model is only briefly described here, but see the accompanying online supplement for a thorough description of the parametric form of the model, the data used to fit the model parameters, and the model manipulation used to generate a RR-CDR difference curve. Conceptually, this curve is generated by changing the PoM score used as the threshold for recall and comparing the RR and CDR to the nominal values using a PoM threshold of 0, which represents screening as it is currently practiced. Changing the PoM threshold allows us to predict the effect of a change in RR on CDR, and to predict the precision of the difference estimates for specified numbers of readers and cases. The values for the model parameters were estimated using data from the Dutch National Breast Cancer Screening Program during the period from 2010 to 2015.

Using this model, Fig. 2 shows the CDR prediction and the resulting uncertainty of the estimates based on acquiring data from 20 radiologists, each reading 2,000 screening exams. As described above, this represented a large but feasible study that could be completed in a reasonable time period, and so we assessed the adequacy of this sample size. The figure assumes that the recall rate is “induced” by adjusting the PoM threshold for recall to achieve a fixed reduction in recall rate (e.g., reduce recall by 0.5%). The resulting curve is given in terms of differences with the nominal rates (RR = 2.37%, CDR = 5.53/1000) with error bars representing the expected 95% confidence interval of these differences. For changes in the recall rate of up to 1%, the standard deviation of the CDR difference is 0.12/1000 or less. This level of precision in the difference justified commencing the study.

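### The primary RR-CDR curve is meant to show the benefit of more recall, but its stated outcome data cover recalled cases only, so the part above the current recall rate is understated or unidentified

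*Protocol article*

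**What the plan says.** **Purpose.** Under Study endpoints in the protocol article, the primary curve should make it possible to determine "the benefit, or lack thereof, in increased number of cancers detected at screening due to an increase in the recall rate".

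**Data for the curve.** The same section says that "constructing this curve involves obtaining the outcome of the cases recommended for recall by each participating radiologist", and that "breast cancer diagnosed within 12 months of the woman being recalled from screening is defined as a screening-detected cancer". Overall study design describes the 1-year source as "short-term (1 year) follow-up of the recalled cases via the screening organization". The Abstract pairs each follow-up with a curve: "Comparison of the results to short- and medium-term follow-up allows for estimation of the RR-CDR and receiver operating characteristics curves, respectively".

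**How the curve is generated.** The sample-size section describes "changing the PoM score used as the threshold for recall and comparing the RR and CDR to the nominal values using a PoM threshold of" (the value is zero, and it stands for current practice). Data acquisition instructs readers to "swipe to the left of center if they did not recall the case, and to the right of center if they did".

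**Outcomes of non-recalled cases.** Study endpoints states, in the paragraph on the secondary ROC curves: "Interval cancer cases will be identified through linkage with the Netherlands Cancer Registry after the necessary waiting period". The Introduction and Overall study design also list this 2-year ascertainment as part of the study, without saying that it feeds the primary curve.

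**The concern.** To move right along the curve, towards more recall, the threshold must drop below 0. The cases that come in are the ones this reader scored left of centre and did not recall. Those are the cases for which the stated primary data source holds no outcome, unless another reader's decision led to recall. A woman whom nobody recalled cannot meet the definition of a screen-detected cancer at all.

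This is partial verification driven by the score under evaluation. Each added case raises the recall rate in full, while its cancer status is known only in part. The confidence intervals would not reveal the resulting bias, because they measure sampling variation.

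The Discussion intends the curve to help select the programme's operating point and to inform guidance to radiologists on recall rates. A right-hand side that is too flat would favour keeping or lowering the recall rate for a reason unrelated to reader performance.

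**Working it through.** **1. Which side of the curve is affected.**
- Threshold above 0 (less recall): the curve drops cases the reader had recalled. Their outcomes are in the primary source, so the problem does not arise.
- Threshold below 0 (more recall): the curve adds cases the reader had not recalled. Their outcomes are not in that source, apart from women recalled through the double-reading process.

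**2. The plan's own precision figure.** The article gives nominal RR 2.37%, CDR 5.53/1000, 20 × 2,000 = 40,000 readings, and an SD of the CDR difference of at most 0.12/1000 for RR changes up to 1%. The model is in a supplement not shown, so the SD cannot be reproduced exactly. As a rough check, with no between-reader variance, SD ≈ √(|ΔCDR|/40,000). An SD of 0.12/1000 then corresponds to ΔCDR = 0.00012² × 40,000 = 0.58/1000, or about 23 cancers. The models in step 3 give SDs of 0.09-0.16/1000 for a 1-point reduction. The stated figure is plausible but not confirmed.

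**3. Size of the true gain (assumed models).** Non-cancer scores are N(0,1) and cancer scores N(μ, s²), forced through RR 2.37% and CDR 5.53/1000. Assumptions not in the article: cancer prevalence π = 7-10/1000 and SD ratio s = 1-2.

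Example with π = 8/1000, s = 1:
- Non-cancer recall fraction = (0.0237 − 0.00553)/(1 − 0.008) = 0.0183, so the current threshold is t₀ = 2.090.
- Sensitivity = 5.53/8 = 0.691, so μ = 2.090 + 0.499 = 2.589.
- RR 3.37% requires t₁ = 1.912, where sensitivity is Φ(2.589 − 1.912) = 0.751.
- Gain = 8 × 0.7508 − 5.53 = 0.48/1000.

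**4. How much of the gain is counted.**
- Own recalls only: every added case is unverified, so the counted gain is 0.
- Own plus partner recalls: two readers' cancer scores are taken as bivariate normal with correlation ρ = 0-0.9 (assumed), with the same threshold, and either recall leading to work-up. The fraction counted is P(partner score > t₀ | own score between t₁ and t₀). In the example with ρ = 0.5 it is 0.594, so 0.476 × (1 − 0.594) = 0.19/1000 is lost.

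| Assumed prevalence per 1000 | True gain per 1000 for +1 point RR (s = 2 to s = 1) | Share counted with partner recalls (over ρ and s) |
|---|---|---|
| 7 | 0.18-0.34 | 50-79% |
| 8 | 0.25-0.48 | 47-69% |
| 9 | 0.31-0.59 | 46-61% |
| 10 | 0.35-0.68 | 44-55% |

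**5. Against the stated SD of 0.12/1000.**
- Own recalls only: the loss is 0.18-0.68/1000, which is 0.18/0.12 = 1.5 to 0.68/0.12 = 5.7 SDs.
- With partner recalls: 21-56% is lost. The smallest loss is 0.177 × 0.21 = 0.04/1000 (0.3 SD) and the largest 0.678 × 0.56 = 0.38/1000 (about 3 SDs).

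**The case against.** The strongest reply is that the article does not exclude other outcomes. It says that building the curve involves the outcomes of recalled cases, and 2-year ground truth for non-recalled cases is a planned stage. The screen-detected definition refers to the woman being recalled, not to recall by the study reader, so partner-recalled cancers can qualify. The 24-month ROC curves are planned, the Introduction says ROC performance can be converted to recall and detection rates given prevalence, and the Discussion allows the operating point to come from either kind of curve. Handling of unverified cases may also be set out in an analysis plan not shown.

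Part of this stands. A reader might infer that the curve must be flat above current practice whatever the truth. That holds only if outcomes come solely from the reader's own recalls and unverified cases are counted as cancer-free; the article states no rule for them. With partner recalls the loss is partial and may be well below one SD.

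A reader might also infer that the Fig. 2 precision for increases in recall is invalid. The figure is not shown and the text describes a reduction, so no claim is made about it. Nor can partner-found cancers be capped by subtracting 5.53 from a programme CDR: the former is a model value fitted to 2010-2015 data, and the programme rates in the Introduction (6.3, 6.7 and 7.0/1000) give differences of 0.8, 1.2 and 1.5/1000.

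What the reply does not remove is the mismatch in the text. The stated use is an increase in recall, the stated data are recalled cases with a recall-based definition, and the Abstract assigns the longer follow-up to the ROC curves. Treating unverified cases as missing, or extrapolating, would not support the stated use either.

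**Conclusion.** The point holds for the half of the primary curve above the current recall rate. From the data the article assigns to it, the CDR gain from more recall is zero (own recalls only), attenuated (partner recalls included), or unidentified or model-dependent (unverified cases missing or extrapolated). The direction of the error in the first two cases follows from the design.

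The sizes rest on assumed prevalence, SD ratio, between-reader correlation and a binormal form, and should be read as orders of magnitude. The attenuated case also assumes that either reader's recall leads to work-up; where consensus or arbitration turns a partner's recall down, more would be lost. The reduction side does not have this problem, and the data needed for a remedy are already being collected. Because the article names an increase in recall as the use of its primary endpoint, the text should be corrected before that analysis is done.

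**What to change.** 1. Limit the 12-month primary curve to thresholds at or above 0, that is, recall rates at or below current practice.
2. For thresholds below 0, build the curve after the planned registry linkage and expert review of interval cancers, and amend the cancer definition for that part. Report a range:
   - low: cancers found after any programme recall;
   - main: those plus interval cancers graded as minimal signs or missed;
   - high: all cancers within 24 months. Call this a high sensitivity estimate and not an upper bound, because cancers that surface after 24 months are still missed.
3. State that no conclusion about raising the recall rate will be drawn from the 12-month recalled-case data alone.

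Cost: wording in the protocol and analysis plan, and later reporting of the right half of the curve, once the 2-year follow-up is complete. No new data are needed.

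### The per-reader recall–detection curve counts cancers by the programme's recall, so cancers in overruled participant recalls drop out of the detection rate while those recalls stay in the recall rate

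*Protocol article*

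**What the plan says.** Three parts of the Protocol article's Materials and methods bear on this.

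- **Unit of analysis.** Study cases states that "all performance estimates are performed at the level of individual readers". Data acquisition makes the reader's recall a matter of the score: "The radiologists were instructed to swipe to the left of center if they did not recall the case", and to the right if they did. The sample-size section treats threshold 0 as current practice.
- **Programme recall.** Study cases also says that the programme "involves independent double reading of all cases with consensus or arbitration for disparate decisions". A participant's recall and the programme's recall are therefore different events.
- **Outcome for the primary curve.** Study endpoints says that the curve requires "obtaining the outcome of the cases recommended for recall by each participating radiologist" and adds: "This data is available through the screening organization". It then adopts the programme rule: "breast cancer diagnosed within 12 months of the woman being recalled from screening is defined as a screening-detected cancer". Overall study design describes the data source as "short-term (1 year) follow-up of the recalled cases via the screening organization".

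The Abstract assigns short-term follow-up to the RR-CDR curve and medium-term follow-up to the ROC curves. Study endpoints likewise places the registry linkage under the secondary ROC endpoints.

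**The concern.** The horizontal axis (RR) belongs to the individual reader, but the numerator of the vertical axis (CDR) depends on what the programme did. When a participant scores a case above 0 and consensus or arbitration decides against recall, the case counts towards that reader's RR. No programme recall follows, so a cancer in it cannot meet the definition. The follow-up named for this curve covers recalled cases only.

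The article says that the outcomes of cases each participant recommended for recall can be had from the screening organization. On its own description, that is assured only for those the programme went on to recall. At stake are the anchor point of the curve and the apparent cancer cost of reducing recall. The Discussion intends the curve for choosing the programme's operating point.

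**Working it through.** **1. The plan's own figure.** The sample-size section gives an SD of the CDR difference of 0.12/1000 or less for recall changes up to 1%, with 20 × 2,000 = 40,000 readings. It comes from a model in a supplement that is not shown, so it cannot be reproduced. As a plausibility check, if only Poisson variation in the moved band mattered, SD = √(ΔCDR/40,000). An SD of 0.12/1000 then implies ΔCDR = 0.00012² × 40,000 = 0.576/1000, or 23 cancers. Nothing contradicts the stated figure. One SD equals 0.00012 × 40,000 = 4.8 cancers.

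**2. Direction, reduced recall.** Let v(t) be the probability that the programme recalled the woman, given cancer and a participant score of t. Under the literal rule the observed slope of CDR at t is the true slope times v(t), and v(t) ≤ 1. Summed over the scores above 0, the nominal CDR is too low or unchanged. Summed over a band removed by raising the threshold, the apparent cancer loss is too small or unchanged.

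**3. Direction, increased recall.** The curve shows differences from threshold 0. Overruled participant recalls lie above 0 at both the nominal and the lowered threshold, so they cancel. Increments on this side depend instead on cancers in women whom neither the participant nor the programme recalled.

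**4. Size of the loss in nominal CDR.** Inputs from the article are RR 2.37%, CDR 5.53/1000, 40,000 planned readings and 42,215 recorded scores. Participant recalls: 40,000 × 0.0237 = 948 (42,215 × 0.0237 ≈ 1,000). Cancers: 40,000 × 0.00553 ≈ 221. The article gives neither the share overruled nor the cancer yield among overruled recalls, so both are assumed. Loss per 1000 = 23.7 × share × yield, with cancers per 40,000 readings in brackets:

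| Share overruled | Yield 0.5% | Yield 2% | Yield 5% |
|---|---|---|---|
| 10% | 0.012 (0.5) | 0.047 (1.9) | 0.119 (4.7) |
| 20% | 0.024 (0.9) | 0.095 (3.8) | 0.237 (9.5) |
| 30% | 0.036 (1.4) | 0.142 (5.7) | 0.356 (14.2) |

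**5. From level to difference.** These are shifts in the CDR level, whereas 0.12/1000 is the SD of a difference. A 1-point reduction removes 1/2.37 = 42% of participant recalls, and only lost cancers in that band bias the difference. Each table entry is therefore an upper bound for the bias in the difference curve.

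**6. Illustration.** A two-reader binormal simulation was calibrated to RR 2.37% and CDR 5.53/1000, with an assumed 24-month cancer prevalence of 7.5 or 9 per 1000 and assumed reader correlations and arbitration rule. The scenarios closest to the programme's reported rates (simulated RR 2.2–2.3%, CDR 6.2–6.5/1000) overrule about 37% of participant recalls, more than the range in the table. For a 1-point reduction the CDR change shrinks:

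- at prevalence 7.5/1000, from −0.73 to between −0.66 and −0.67/1000;
- at prevalence 9/1000, from −0.95 to between −0.81 and −0.85/1000.

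That is 8–14% flatter, or about 0.5–1.1 planned SDs. Stricter arbitration gives 27–40%, but with a simulated programme RR of only 1.0–1.4%, well below the 2.23–2.43% in the Introduction. For a 1-point increase at prevalence 7.5/1000, overruled recalls change nothing (+0.41 with and without them). The cancers in women nobody recalled take it from +0.41 to about +0.26/1000.

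**7. If overruled cases were excluded instead.** With 20% overruled, 948 × 0.2 ≈ 190 records go. RR at threshold 0 becomes 758/39,810 = 1.90% instead of 2.37%, so the anchor is no longer the reader's recall rate. If overruled recalls have a lower yield than upheld ones, the curve also becomes too steep.

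**The case against.** The strongest reply is that the article never says overruled cases are counted as free of cancer or that these women had no work-up. Both are inferences from Study cases, Study endpoints and Overall study design. Results expects a small percentage of records to be excluded, partly because a final outcome cannot be obtained, and overruled cases might be among them. This stands as a caution about wording. It does not remove the problem, because exclusion distorts the curve too (step 7).

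A second reply is that handling of discordant cases belongs in an analysis plan and that registry linkage is already planned. The linkage would reveal some of these cancers. But the article itself fixes the definition and the data source for the primary curve, and it assigns the linkage to the ROC curves. The difficulty lies in what is stated.

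A reader might also infer that the whole curve is flattened around current practice, or that cutting recall would look free of cancer loss. The documents do not support either. Overruled recalls cancel from the increments above current recall, the direction that Study endpoints stresses. Nothing in the article shows where these cases lie on the score scale, and the illustration gives a partial loss of slope.

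A reader might go on to replace the primary outcome with any cancer dated from screening, for every rated case. That would count interval cancers that were not visible, which Study endpoints puts at about half, and would blur the primary endpoint with the secondary ROC endpoint.

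**Conclusion.** The point holds on a literal reading. The primary curve combines a reader-level recall with a programme-level detection rule, and the error has a known direction: the nominal CDR, and the cancers lost when recall is reduced, can only be understated. More readings will not shrink it, and the stated SD does not cover it.

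Its size is not established. Under overrule shares of 10–30% and yields of 0.5–5%, all assumed, the nominal CDR loses about 0.01–0.36/1000. The bias in the difference curve lies between zero and that loss, so it runs from negligible to at most about three planned SDs (0.36/0.12). The increased-recall side is not affected by overruled participant recalls. It has its own dependence on cancers in women whom nobody recalled.

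**What to change.** 1. Keep the programme definition for the main curve, so that it remains comparable with the programme's published rates, and state that its CDR is conditional on programme recall.
2. State how participant-positive, programme-negative cases enter RR and CDR, and whether any are excluded for lack of an outcome. Report their number and their score distribution.
3. Present a second version of the curve that also counts cancers in those cases found by the planned registry linkage within 24 months of screening, optionally leaving out those the expert panel grades as not visible.
4. Say in the text that increments above current recall depend on cancers in women whom neither the participant nor the programme recalled.

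The cost is wording, one tabulation and use of a linkage already planned. The second version must wait for that linkage. It may include some cancers that work-up at screening would not have found, so the two versions bracket the answer, apart from any cancers that surface only after 24 months.
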